# Mechanical suppression of osteolytic bone metastases in advanced breast cancer patients: a randomised controlled study protocol evaluating safety, feasibility and preliminary efficacy of exercise as a targeted medicine

**DOI:** 10.1186/s13063-018-3091-8

**Published:** 2018-12-20

**Keywords:** Tumour suppression, Tumour growth, Resistance training, Aerobic training, Isometric training, Muscle activity, Exercise medicine, Advanced cancer, Bone metastases

## Abstract

**Background:**

Skeletal metastases present a major challenge for clinicians, representing an advanced and typically incurable stage of cancer. Bone is also the most common location for metastatic breast carcinoma, with skeletal lesions identified in over 80% of patients with advanced breast cancer. Preclinical models have demonstrated the ability of mechanical stimulation to suppress tumour formation and promote skeletal preservation at bone sites with osteolytic lesions, generating modulatory interference of tumour-driven bone remodelling. Preclinical studies have also demonstrated anti-cancer effects through exercise by minimising tumour hypoxia, normalising tumour vasculature and increasing tumoural blood perfusion. This study proposes to explore the promising role of targeted exercise to suppress tumour growth while concomitantly delivering broader health benefits in patients with advanced breast cancer with osteolytic bone metastases.

**Methods:**

This single-blinded, two-armed, randomised and controlled pilot study aims to establish the safety, feasibility and efficacy of an individually tailored, modular multi-modal exercise programme incorporating spinal isometric training (targeted muscle contraction) in 40 women with advanced breast cancer and stable osteolytic spinal metastases. Participants will be randomly assigned to exercise or usual medical care. The intervention arm will receive a 3-month clinically supervised exercise programme, which if proven to be safe and efficacious will be offered to the control-arm patients following study completion. Primary endpoints (programme feasibility, safety, tolerance and adherence) and secondary endpoints (tumour morphology, serum tumour biomarkers, bone metabolism, inflammation, anthropometry, body composition, bone pain, physical function and patient-reported outcomes) will be measured at baseline and following the intervention.

**Discussion:**

Exercise medicine may positively alter tumour biology through numerous mechanical and non-mechanical mechanisms. This randomised controlled pilot trial will explore the preliminary effects of targeted exercise on tumour morphology and circulating metastatic tumour biomarkers using an osteolytic skeletal metastases model in patients with breast cancer. The study is principally aimed at establishing feasibility and safety. If proven to be safe and feasible, results from this study could have important implications for the delivery of this exercise programme to patients with advanced cancer and sclerotic skeletal metastases or with skeletal lesions present in haematological cancers (such as osteolytic lesions in multiple myeloma), for which future research is recommended.

**Trial registration:**

anzctr.org.au, ACTRN-12616001368426. Registered on 4 October 2016.

**Electronic supplementary material:**

The online version of this article (10.1186/s13063-018-3091-8) contains supplementary material, which is available to authorized users.

## Background

Bone metastases are generally incurable and clinically problematic, yet are present in over 80% of patients with advanced breast cancer [1, 2], representing a debilitating stage of disease with very poor patient prognoses during palliation, and one of the leading causes of breast cancer mortality among women worldwide [3–5]. Osteolytic (lytic) bone metastases, in particular, present a considerable challenge to patients and clinicians due to rapid microarchitectural deterioration of affected skeletal sites through tumour-driven dysregulation of bone metabolic activity in favour of excess resorption [1, 6, 7]. Metastatic breast carcinomas commonly deposit in trabecular (cancellous) regions of bone [6, 8–10], such as the skull, ribs, spine, pelvis and proximal and distal segments of long bones, owing to their strong affinity to red bone marrow [2, 7, 9, 11]. Of direct relevance, the majority of these skeletal structures are characteristically load-bearing [12–14], thus any accelerated bone loss and heightened fragility following tumoural infiltration [8, 10, 15–17] has immediate consequences for patients with cancer if left untreated or unmanaged. Consequently, this destructive skeletal process leads to increased patient morbidity and mortality, with heightened fragility, increased risk of spinal compression, potential development of hypercalcaemia, increased bone pain and increased fracture risk [7, 17–19]; whilst simultaneously creating a localised microenvironment conducive to tumoural growth and invasion within affected bone sites [20–23].

Chemotherapy, hormone therapy, radiotherapy and anti-resorptive medications are the primary therapeutic agents used in breast cancer palliation to delay disease progression, alleviate bone pain and associated symptoms, preserve skeletal integrity and extend survival [24–32]. Whilst effective, these treatments produce well-documented side effects to varying degrees, which can lead to dose limitation or cessation, subsequently restricting their full clinical utility. For example, patients with advanced breast cancer with bone metastases are provided with bone strengthening (anti-resorptive) medications such as bisphosphonates or denosumab to fortify bone through induced sclerosis leading to increments in bone density [33, 34]. While efficacious in the mid-term; long-term use of these medications themselves eventually generate skeletal fragility in the absence of a discontinuation period [35–37], which is not a clinically viable option for patients with advanced cancer and osteolytic bone metastases.

Bone is highly adaptive and osteogenically sensitive to its mechanical environment, principally through muscular contraction of neighbouring muscle, but also from impact and gravitational forces acting upon the skeleton during human movement and from external loads [12, 38, 39]. Up-regulation of osteoblastic activity through exercise may therefore allow mechanically driven regulation of bone metabolism (i.e. osteocyte-mediated coupling of osteoblast and osteoclast activity) to counteract tumour-driven dysregulation which could have two key benefits: (1) to preserve bone strength through anabolic morphological (material and structural) adaptations; and (2) to interfere with tumoural processes that blunt osteoblastic formation and promote osteoclastic resorption, thus potentially suppressing tumour growth in affected skeletal sites. Preclinical studies [8, 13, 40, 41] have explored this potential relationship in rodent orthotopic models, implanting human breast cancer cells into trabecular skeletal tissue in order to induce osteolysis in the load-bearing tibia. Impressively, when comparing loaded and non-loaded tumour-affected tibiae within host rodents, repeated bouts of externally controlled mechanical compression preserved skeletal integrity (0% versus 71% degradation for loaded and unloaded conditions), blunted tumour-mediated osteolysis, and significantly suppressed tumour growth by approximately 80% [8, 13] in the absence of muscular influence. In addition to osteocyte-driven osteogenic signalling, the inextricable anatomical, mechanical, metabolic and pleiotropic link between muscle and bone [12, 38, 42, 43] provides another avenue of therapeutic osteogenic and anti-tumour potential not yet explored [14, 44–47]. The voluntary activation of muscle surrounding skeletal lesions may deliver anabolic cytokines and myokines (secretome cross-talk) to lesion sites [14, 44, 45, 48] to countenance catabolic tumour-mediated processes [46, 47, 49, 50]. Accordingly, mechanical signals propagated by muscle contraction may concurrently stimulate osteocyte-mediated metabolic activity and myokine-cytokine secretome cross-talk to promote osteogenesis while modulating tumoural behaviour and biology in order to slow tumour growth [14, 45, 48–51].

Human clinical trials have yet to be implemented in this space, owing to a historical and misplaced belief that patients with advanced cancer and bone metastases should be excluded from exercise programmes and synonymous research due to increased risk of skeletal complications or other potential adverse events [52–54]. Formative work by [name] and colleagues [51, 55–58] demonstrated the safety and feasibility of delivering supervised exercise to patients with advanced prostate cancer and bone metastases, avoiding exercises that placed direct or targeted stress on bones with identified lesions. Separate work by Rief and colleagues [59, 60] demonstrated the safety and feasibility of physiotherapy-instructed spinal isometric training in isolation for patients undergoing palliative radiation therapy for spinal bone metastases, though in a small cohort of heterogeneous patients with cancer and disparate lesion types. Taken together, these studies illustrate the potential for preclinical studies to be translated to human patients; specifically models of advanced breast cancer with osteolytic bone metastatic disease. This is particularly important as animal studies do not always translate to the human condition, particularly in exercise-mediated bone adaptation studies, often due to poorly designed human trials for equivalency [12, 61–63].

Given that bone metastases remain one of the leading causes of breast-cancer-related deaths worldwide, additional and novel interventions to target osteolytic lesions in skeletal tissue are highly clinically relevant. Expanding on our prior work, the aim of this study is to (1) assess the safety and feasibility of a supervised and individually tailored resistance, aerobic and flexibility exercise programme that includes targeted spinal isometric training in patients with advanced breast cancer and osteolytic bone metastases; (2) explore the preliminary efficacy of the exercise programme to slow tumour growth and tumour biomarker activity in target osteolytic spinal lesions and (3) examine the broader efficacy of the exercise programme to preserve muscle and bone mass, improve physical fitness, enhance physical function, reduce cancer-related fatigue and increase quality of life. It is the working hypothesis of this study that the exercise programme will be safe and feasible; will show signs of tumoural suppression and/or favourable alterations in tumour biomarkers; and will lead to positive physical and psychosocial outcomes for patients. If successful, the outcomes of this trial will be used to improve clinical knowledge pertaining to exercise prescriptions for patients with advanced cancer who have metastatic carcinomas and high disease burden, and will be used as a foundation for future phase II and phase III efficacy-focused human clinical trials to establish the anti-cancer effects of exercise. It is anticipated that this new information will aid in the establishment and/or renewal of clinical exercise guidelines for the management of cancer across the disease spectrum.

## Methods

### Study design

This single-blinded (investigators blinded to group allocation), two-armed, randomised and controlled (supervised exercise versus usual medical care) explorative clinical trial will examine the feasibility, safety and preliminary efficacy of combining targeted spinal isometric training with modulatory, multi-modal exercise (M3EP-SIT) in women with advanced breast cancer and stable osteolytic spinal bone metastases. The exercise group (intervention arm) will receive an individually tailored and supervised 12-week exercise programme involving resistance, aerobic, flexibility and isometric exercises in addition to usual medical care. The control group will receive usual medical care only during this time and will be asked not to change their baseline levels of physical activity. However, following the trial, the control group will be offered the same exercise programme if proven to be safe and efficacious. This procedure has been shown to be an effective strategy to minimise study contamination, patient withdrawal or loss of patients to follow up in prior exercise oncology trials [14, 52, 64–68].

### Recruitment

Patients will be recruited by invitation of their cancer specialist (surgeon, radiation oncologist or medical oncologist) who will provide clinically eligible patients with a study information sheet and refer these patients to an independent study coordinator. If patients are interested in participation and their eligibility is confirmed, they will receive an informed consent document to read and sign in the presence of a study investigator and clinical research coordinator before undertaking baseline measurements prior to randomisation (Fig. 1).

**Fig. 1 Fig1:**
[figure not shown]
Schematic overview of the study protocol. MRI, magnetic resonance imaging; DXA, dual-energy x-ray absorptiometry; pQCT, peripheral quantitative computed tomography; 1RM, one-repetition maximum

### Randomisation

Patients will be randomly allocated in a ratio of 1:1 to the two study arms: exercise or usual care, stratified by age (≤ 60 years, > 60 years), hormone receptor (HR) status (HR+, HR-) [69] and time since completion of palliative radiotherapy to target spinal lesions (< 3 months, ≥ 3 months) and/or time since commencing or changing hormone therapy and/or chemotherapy (< 3 months, ≥ 3 months). A research officer with no patient contact will be responsible for randomisation of patients into either group using a computer-generated code through a random-assignment programme. Study investigators and exercise physiologists conducting testing procedures will be blinded to group allocation. Only exercise physiologists outside the research team will be permitted to deliver the exercise intervention to participants in order to maintain integrity of the blinding process.

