### Participants

A total of 40 women (20 subjects per arm) with breast cancer and stable osteolytic bone metastases in cervical, thoracic and/or lumbar vertebrae will be invited to participate. They will be included if they have not engaged in regular exercise in the past 3 months (defined as undertaking structured aerobic and/or resistance training two or more times per week). Due to the novelty of this explorative clinical trial, our sample size is based on previous preclinical animal studies [13, 70–72], human pilot studies [14, 56, 58, 73, 74] and consideration of the ability to recruit patients with advanced breast cancer and osteolytic bone metastases during the trial. Specifically, to achieve 80% power at an alpha level of 0.05 (two-tailed), 16 subjects per group are required to demonstrate a meaningful difference (effect size ≥ 1.0) at the completion of the study for the primary endpoint, and most secondary endpoints. To account for an attrition rate of up to 25%, 40 subjects will be randomised equally between the study arms (exercise, *n* = 20; control, *n* = 20).

Patients are permitted to receive radiotherapy for non-spinal bone metastases while enrolled in this trial. Patients require medical clearance prior to enrolment, therefore must achieve an Eastern Cooperative Oncology Group (ECOG) performance status ≤ 1, and must not have any acute illness, significant bone pain or cardiovascular or neurological disorders that could inhibit exercise participation as judged by their managing physician. All participants must provide written informed consent prior to participation. Patients will be excluded from this trial if they are receiving experimental treatments. The protocol has been approved by the Human Research Ethics Committee (HREC) of Edith Cowan University (ECU), Project ID 14266 [name]; St John of God Hospitals (SJOG), Project ID 969 and Sir Charles Gairdner and Osborne Park Health Group (SCGOPHG), Project ID 2016–118. This trial is also registered with the Australia and New Zealand Clinical Trails Register (ANZCTR), Trial ID ACTRN-1261600136842.

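### The treatment-timing stratifier is joined by and/or, so some eligible patients fall in both of its levels and others in none

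*Protocol article*

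**What the plan says.** The Randomisation section of the protocol article fixes a 1:1 ratio and names the stratifiers. Age is split at 60 years and hormone receptor status into positive and negative. The third item is "time since completion of palliative radiotherapy to target spinal lesions", under 3 months against 3 months or more. It then runs on, "and/or time since commencing or changing hormone therapy and/or chemotherapy", with the same two levels. The section does not say whether the timing items form one factor or several. It gives no rule for timings that disagree, and no level for a patient who never had one of the treatments. The allocation method is described only as a computer-generated code from a random-assignment program.

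The Participants section says that "40 subjects will be randomised equally between the study arms", 20 in each. It does not require earlier radiotherapy to the target lesion, or current hormone therapy or chemotherapy. The Statistical analysis section plans a group-by-time repeated-measures analysis of variance, with analysis of covariance where appropriate.

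**The concern.** A stratification factor needs levels that are exhaustive and mutually exclusive, because the allocation program must receive exactly one value per patient before it releases an assignment. These levels are neither. This is a fault in a rule that the article states, not a detail left to a fuller document.

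The factor also matters. The second aim of the trial is to explore whether exercise slows tumour growth and tumour biomarker activity over about 13 weeks. Radiotherapy to the target lesion, or a drug change, shortly before baseline is an obvious rival explanation for a change in lesion volume or biomarkers. If different staff resolve the wording differently, the recorded stratum means different things for different patients. It then serves poorly both for allocation and for later adjustment.

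**Working it through.** **1. Can every eligible patient be placed?** Four hypothetical patients, none ruled out by the Participants section:

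| Patient | Read as one timing factor | Read as two (radiotherapy; systemic) |
|---|---|---|
| Irradiated 5 months ago, hormone therapy changed 1 month ago | both levels | placed: ≥ 3 and < 3 |
| Target lesion never irradiated, hormone therapy started 6 months ago | placed: ≥ 3 | no radiotherapy level |
| Irradiated 6 months ago, hormone therapy unchanged for a year, chemotherapy started 2 months ago | both levels | systemic factor has both levels |
| Never irradiated, on neither systemic therapy | no level | no level on either factor |

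The third patient fails because of the second and/or, between hormone therapy and chemotherapy. Splitting those into two factors would place her, but would leave anyone not on one of the treatments without a level. No reading places all four patients. This step needs no assumption about prevalence.

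**2. How many cells?** The count is the product of the factor levels, and 40 divided by it is the mean per cell.

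- One timing factor: 2 × 2 × 2 = 8 cells, 40/8 = 5 patients each.
- Two timing factors: 2 × 2 × 2 × 2 = 16 cells, 40/16 = 2.5 each.
- Hormone therapy and chemotherapy also separate: 32 cells, 40/32 = 1.25 each.
- Two timing factors with a not-applicable level on one or both: 2 × 2 × 3 × 2 = 24 or 2 × 2 × 3 × 3 = 36 cells.

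**3. What would that do to the 20:20 split?** The article names no mechanism, so this step is conditional on permuted blocks within fully crossed cells. Simulation of 40 patients; assumed prevalences, not in the article, are age 50/50, hormone receptor positive 75%, timing 50/50.

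| Scheme | Exactly 20:20 | 22:18 or worse |
|---|---|---|
| 8 cells, blocks of 2 | 39% | 12% |
| 8 cells, blocks of 4 | 29% | 24% |
| 16 cells, blocks of 2 | 29% | 26% |
| 16 cells, blocks of 4 | 22% | 39% |
| Simple randomisation | 13% | 64% |
| Minimisation on four factors and the overall total, biased coin 0.8 | 63% | 2% |

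Equal cell probabilities give nearly the same: with blocks of 4, exactly 20:20 in 31% (8 cells) and 21% (16 cells). With 16 cells and blocks of 4, about 11.5 of the 16 cells hold less than one full block.

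**4. Does an unequal split cost power?** The article's planning figure is 16 per group for effect size 1.0, two-sided 0.05 and 80% power. The normal approximation reproduces it: 2 × (1.960 + 0.842)² / 1² = 15.7, so 16; and 16 × 1.25 = 20 per arm, 40 in all. With all 40 analysed by a two-sample t test at effect size 1.0, power is 86.9% at 20:20, 86.1% at 17:23 and 85.5% at 16:24. The loss from 20:20 to 16:24 is 86.9 − 85.5 = 1.4 percentage points.

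**The case against.** The strongest reply is that this is a small wording slip in a condensed article. The list reads most naturally as three factors, and a sensible coordinator would count a patient as recent if any listed event fell within 3 months. Lesion volume and biomarkers are secondary outcomes in a pilot aimed mainly at feasibility and safety. Analysis of covariance is already allowed for, and health history and concomitant medications are collected at baseline.

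Much of this stands, and it limits the point. It does not remove it: the sensible reading is a guess, the text does not state it, and the levels as printed do not produce it.

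A reader might also infer four stronger things, which the documents do not support:

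- *That the randomisation cannot deliver 20:20.* This presumes crossed permuted blocks. The article names neither blocks nor a block size and does not exclude minimisation, which came within 19:21 in 98% of simulated trials on four factors. An article may leave such details to the full protocol, so their absence is no finding. Every stratified scheme in the table also came closer to equal arms than simple randomisation.
- *That the plan breaks a promise of covariate balance.* It states an equal split. Balance on the factors is the usual purpose of stratifying, but no sentence promises it.
- *That therapy timing would be the worst-balanced factor.* With equal cell probabilities all factors behave alike. Its weakness is that it is undefined.
- *That timing cannot be adjusted for.* It can, once it is defined and the treatment dates are recorded.

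**Conclusion.** The concern holds as a defect of definition. The timing stratifier is not mutually exclusive, not exhaustive, and unclear in number: 8 cells if it is one factor, 16 if two, and more on other readings. This follows from the text alone.

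The consequence for arm sizes is conditional. If permuted blocks within crossed cells are used, an exact 20:20 split is not assured: about 22–39% of simulated trials with 8 to 16 cells and blocks of 2 or 4. Those percentages rest on assumed prevalences and an assumed mechanism. Even then the cost in power is trivial, at most 1.4 points down to a 16:24 split. What is at risk is the usefulness of the stratum for the exploratory lesion-volume and biomarker comparison, not the size of the trial or its feasibility and safety aims. The correction should be made before any further allocation.

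**What to change.** Replace the and/or wording in the Randomisation section with one yes/no factor. Yes: radiotherapy to a target spinal lesion completed, or hormone therapy or chemotherapy started or changed, within the last 3 months. No: everyone else, including patients who never had these treatments. With age and hormone receptor status this gives three binary factors and 8 cells, and it places each of the four example patients once (yes, no, yes, no). Record the underlying treatment dates at baseline. For anyone already randomised, leave the allocation as it stands and derive the factor from those dates.

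In the Statistical analysis section, name the same three factors as covariates in the between-group comparison.

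The costs are small. The allocation program must be re-specified, with nothing new asked of patients beyond treatment dates. A single factor gives up separate control of radiotherapy timing and systemic-therapy timing. Three covariates use three degrees of freedom: in a two-group comparison of 40 patients the residual falls from 38 to 35, and with 32 completers (16 per arm) from 30 to 27.

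Minimisation with a random element over the three factors would bring the arms closer to equal, but it is an option for the sponsor, not a required correction.

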#### Primary Endpoint

##### Feasibility

Study and programme feasibility will be quantified through a series of multi-item categories including patient recruitment and trial completion, patient safety and tolerance and program adherence and compliance (Table 2). Programme safety will be assessed by recording the incidence and severity (grading) of adverse events and/or skeletal complications [18] throughout the on-trial period for the intervention and control arms in accordance with the common terminology criteria for adverse events (CTCAE) v5.0 criteria. Skeletal complications will include heightened bone pain at sites of known bone metastases and/or pathological skeletal fractures. The nature, severity and impact of bone pain will be examined using the Functional Assessment of Chronic Illness Therapy (FACIT) bone pain questionnaire at baseline and post intervention.

**Table 2 Tab2:** Schedule of assessments at baseline and post intervention

Measures	Baseline	Post intervention
Tumour morphology (off-site)		
- MRI: T1-axial	X	X
Tumour biomarkers		
- Blood: HIF-1α, TGF-β	X	X
Anthropometry		
- Height (cm)	X	
- Weight (kg)	X	X
- Waist circumference (cm)	X	X
- Hip circumference (cm)	X	X
- Femoral length (mm)	X	
- Tibial length (mm)	X	
- Body mass index (kg/m^2^)	X	X
- Waist-to-hip ratio	X	X
Body composition		
- DXA: whole-body, spinal, hip	X	X
- pQCT: femoral, tibial	X	X
Physical assessments		
- NeuroCom Balance Test	X	X
- 1RM Strength Test (Leg Extension)	X	X
- 400 m Walk Test	X	X
- Timed Up and Go Test	X	X
Other biomarkers (off-site)		
- Blood: P1NP, ALP, CRP, fasting glucose and lipids	X	X
- Urine: NTx	X	X
Questionnaires		
- Demographic and health history	X	
- Concomitant medications	X	X
- Health-related quality of Life (SF-36)	X	X
- Cancer-specific quality of life (EORTC: QLQ30, BR23)	X	X
- Bone Pain (FACIT-BP)	X	X
- Brief Symptom Index (BSI-18)	X	X
- Insomnia Severity Index (ISI)	X	X
- Godin Leisure-time Exercise	X	X
Exercise programme		
- Clinic exercise record sheet (prescribed vs. actual)	At each exercise session	
- Home exercise record sheet (prescribed vs. actual)	At each exercise session	
- Pre-session bone pain, muscle soreness and fatigue (VAS)	At each exercise session	
- Post-session rating of perceived exertion and tolerance (VAS)	At each exercise session	

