##### Biomarkers

Metastatic tumour biomarkers, hypoxia-inducible factor 1-alpha (HIF-1α) and transformation growth-like factor beta (TGF-β) will be serologically examined to measure tumoural hypoxic activity and growth activity respectively; identified as synergistic drivers of metastatic tumour progression [45, 80–84]. Fasted serological and first-void samples for urianalysis will also be collected within 48 h of baseline and post-intervention testing sessions to measure bone metabolic activity and systemic inflammation. Specifically, bone formation marker, amino-terminal propeptide of type 1 procollagen (P1NP); bone resorption marker, amino-terminal collagen type-I telopeptide (NTx); bone disorder marker, alkaline phosphatase (ALP), inflammation marker, C-reactive protein (CRP) and fasting glucose and lipid profiles will be examined. All fasted serological and first-void biomarkers will be collected in the morning, and assessed by the same accredited laboratory (Australian Clinical Laboratories, Perth, Western Australia).

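### The three-month treatment window used for stratification leaves out anti-resorptive drugs, which act on the trial's bone endpoints; the cost is precision and possible chance imbalance, and one prespecified covariate would recover most of it

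*Protocol article*

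**What the plan says.** The Randomisation section allocates 40 women 1:1, stratified by age (two levels), hormone receptor status (two levels), how recently palliative spinal radiotherapy ended (cut at three months) and/or a systemic-treatment item worded as "time since commencing or changing hormone therapy and/or chemotherapy (< 3 months, ≥ 3 months"). Anti-resorptive drugs do not appear.

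The Background lists four classes of treatment for this population: "Chemotherapy, hormone therapy, radiotherapy and anti-resorptive medications are the primary therapeutic agents used in breast cancer palliation". It adds that patients with bone metastases are provided with "bisphosphonates or denosumab to fortify bone through induced sclerosis leading to increments in bone density".

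The Biomarkers section makes P1NP (formation), ALP and the "bone resorption marker, amino-terminal collagen type-I telopeptide (NTx") secondary endpoints. The Musculoskeletal health section adds DXA areal density and content, and pQCT volumetric density. Preserving bone mass is part of the third study aim.

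Three other places bear on the point:
- Participants excludes women on experimental treatments and sets no condition on anti-resorptive use or timing.
- Table 2 lists "Concomitant medications" at baseline and post intervention, without saying how the record will be used.
- Statistical analysis allows analysis of covariance where appropriate and names no covariate.

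**The concern.** The recency window covers three of the four treatment classes that the article calls primary. The one left out acts most directly on bone turnover and bone density. As the article is written, a woman who began a bisphosphonate or denosumab shortly before baseline is eligible and is treated the same as a woman established on it for years.

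In the recent starter, part of the change from week 0 to week 13 in a resorption marker may be the drug's effect. That adds between-patient variation unrelated to exercise. In a trial of this size, recent starters may also fall unevenly between the arms. The article claims 80% power for most secondary endpoints, and the pilot is meant to inform phase II and III trials. A blurred bone signal would therefore carry forward.

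**Working it through.** **The plan's own figure.** For effect size 1.0, two-sided alpha 0.05 and 80% power: n per group = 2 × (1.960 + 0.842)² / 1.0² = 15.7, so 16. This reproduces the stated 16 per group. Under the t distribution, power at 16 per group is 78%.

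**Which variance matters.** With two time points, the group × time test is a comparison of change scores, so the relevant quantity is the variance of the change in NTx.

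**Inputs.**
- From the article: 40 randomised, 20 per arm.
- Assumed, because the documents give none of these: share of recent starters or changers p = 10–30%; extra fall in NTx among them f = 40–60 percentage points; residual SD of NTx change s = 25, then 40 and 50.

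**Precision.** If the factor is ignored, the variance inflation is 1 + p(1 − p)f²/s².

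| p | f | s = 25 | s = 40 | s = 50 |
|---|---|---|---|---|
| 0.1 | 40 | 1.23 | 1.09 | 1.06 |
| 0.2 | 60 | 1.92 | 1.36 | 1.23 |
| 0.3 | 60 | 2.21 | 1.47 | 1.30 |

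Worked case: p = 0.2, f = 60, s = 25 gives 1 + (0.2 × 0.8 × 3600)/625 = 1 + 576/625 = 1.92.

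If effect size 1.0 is taken on the residual SD, t-test power at 16 per group drops from 78% to about 69%, 51% and 45% for inflation factors of 1.23, 1.92 and 2.21.

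**Chance imbalance.** Take 8 recent starters among 40 women (p = 0.2), allocated 20:20 without regard to this factor. By the hypergeometric distribution, P(4:4) = 0.305 and P(5:3 or 3:5) = 0.460, so a split of 6:2 or worse has probability 1 − 0.765 = 0.235. A 6:2 split with f = 60 moves the group difference by (6/20 − 2/20) × 60 = 12 points.

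**Is that bias?** With s = 25, the total SD is √(625 + 576) = 34.7 and the standard error of the difference is 34.7 × √(2/20) = 10.96. The 12-point shift is about 1.1 standard errors. Simulating this scenario with no exercise effect, an unadjusted t-test rejects about 5% of the time over all allocations, and about 11% of the time given a 6:2 split.

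**Would another stratum help?** The existing factors make 2³ = 8 cells (5 women each on average) if the timing items form one factor, or 2⁴ = 16 cells (2.5 each) if they form two. A further two-level factor would make 16 to 32 cells, or 2.5 down to 1.25 women each. That is too sparse.

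**The case against.** Several objections deserve weight.

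- **Covariates belong in the analysis plan.** The article collects medication data and leaves room for covariance analysis. This stands as far as an unnamed covariate list goes, which is no fault by itself. It does not dispose of the point: the article does fix its recency factors, with cut-points, and that fixed choice leaves out a class its own Background singles out.
- **The stratification sentence is not wrong.** This stands. The Background describes the population and does not promise balance on anti-resorptives. Limiting the factors in a 40-patient trial is also defensible. The gap is better closed in the analysis than in the randomisation.
- **The size rests on assumed inputs.** This also stands. The residual SD matters greatly, as the table shows. The calculation gives every recent starter or changer the full fall, although a woman who began weeks before baseline may already have a lowered baseline value, and one who switches agents does not go from untreated to treated. The figures therefore lean towards the high side. The article states the density effect but gives no size or time course. The marker effect is inferred from the drug class and from NTx being called a resorption marker.
- **The endpoints are secondary.** The trial is principally about feasibility and safety, and no primary conclusion changes.

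Two stronger readings are tempting. A reader might infer that the omission manufactures a false exercise effect. The documents do not support this: allocation is random, and the overall error rate stays near 5%. A reader might also extend the point to the sentence "Patients are permitted to receive radiotherapy for non-spinal bone metastases while enrolled in this trial", since the markers are systemic. Nothing in the article says such treatment alters these markers, and it falls after randomisation, where no baseline window could cover it.

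**Conclusion.** The point holds as one of efficiency and chance imbalance on secondary endpoints. It is not a systematic bias, and the protocol does not contradict itself. The recency window omits the treatment class most relevant to NTx, P1NP, ALP and the DXA and pQCT bone measures, and nothing else in the article makes up for it.

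For NTx, under the stated assumptions, the variance of change rises about 1.2- to 2.2-fold at a residual SD of 25, and about 1.1- to 1.5-fold at SD 40. An imbalance of 6:2 or worse has probability 0.235 if 8 of 40 women are recent starters. No size can be given for bone density. The change is worth making because it is cheap, although the trial's primary conclusions do not depend on it.

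**What to change.** From the baseline concomitant-medication form, code one yes/no item: anti-resorptive started or changed within three months before baseline. The form should capture the agent and its start or change date. Prespecify this item, together with the baseline value of the outcome, as a covariate in the analyses of NTx, P1NP, ALP and the DXA and pQCT bone outcomes. Leave the randomisation strata as they are.

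Report on-trial anti-resorptive starts and changes by arm. Do not use them as a covariate. Label any analysis that excludes those women as exploratory, because it conditions on an event after randomisation that the exercise programme could itself influence, for example through bone pain.

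The cost is one coded item and one degree of freedom for it in each bone analysis. The covariate recovers only the variation due to recent starts before baseline; on-trial starts stay in the residual.
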